### Evaluation and outcomes

Participants in the study will undergo clinical evaluation and laboratory testing, as outlined in online supplemental table 1. The collected data will include demographic information such as age and gender, disease diagnosis and progression, interventions and prognosis, as well as adverse events (AEs). The disease diagnosis data will encompass primary and concomitant diseases, blood culture results, white blood cell count and liver and kidney biochemistry. Disease progression data will involve baseline severity scores and serum biomarkers, including Sequential Organ Failure Assessment (SOFA) score, Acute Physiology and Chronic Health Evaluation II (APACHE II) score, procalcitonin (PCT), high-sensitivity C-reactive protein (hs-CRP), interleukin 2 (IL-2), IL-4, IL-6, IL-10, tumour necrosis factor-α (TNF-α) and interferon-γ (IFN-γ). Follow-up values on specific days (day 1 (D1), D3, D5, D7) after randomisation will also be recorded, along with the changes from baseline.

10.1136/bmjopen-2023-072897.supp2Supplementary data

Data related to disease intervention will include the requirement and duration of life support measures like mechanical ventilation, vasoactive drugs and continuous renal replacement therapy. Disease prognosis data will encompass 28-day all-cause mortality, ICU mortality, in-hospital mortality, incidence of new-onset acute kidney injury (AKI) after ICU admission, ICU stay and length of hospital stay. Throughout the study, data on organ dysfunction, occurrence of AKI and safety events will be continuously monitored.

The primary efficacy endpoint of the study is 28-day all-cause mortality. The secondary efficacy endpoints are as follows:

ICU mortalityHospital mortalityDuration of ICU and hospital stayIncidence of new AKI in ICUSOFA/APACHE II scores on specific days (D1, D3, D5 and D7) and their changes from baseline (ΔSOFA/ΔApache II)Demand and duration of life support measures (vasopressors, invasive mechanical ventilation and continuous renal replacement therapy).Lactate concentration of arterial blood on specific days (D1, D3, D5 and D7) and their changes from baseline (ΔLAC).Levels of PCT, hs-CRP, IL-2, IL-4, IL-6, IL-10, TNF-α and IFN-γ on specific days (D1, D3, D5, and D7) and their changes from baseline.The detection of levels of IL-2, IL-4, IL-6, IL-10, TNF-α, and IFN-γ is not mandatory if unavailable.

The safety endpoint of the study includes the assessment of any AEs, including serious adverse events (SAEs) and adverse drug reactions (ADRs). These ADRs may manifest as various symptoms, such as head swelling, dyspnoea, convulsion, diplopia, purpura, bleeding tendency, allergies, and others.

During clinical research, it is essential for researchers to closely observe any AEs experienced by subjects. When AEs are identified, researchers should promptly take appropriate measures based on the subjects’ conditions. Regardless of whether the AEs are associated with LA injection or not, it is necessary for researchers to diligently record them in detail within the case report form (CRF). The recorded information regarding AEs should encompass a description of the events, their occurrence time, severity, duration, measures taken, final results and outcomes. These records serve the purpose of analysing the potential correlation between AEs and LA injection, and they need to be signed and dated. In the event of encountering any SAEs, it is mandatory to report them to the principal investigator of the trial, the ethics committee (EC) and the state supervision agency within 24 hours of their occurrence. When an AE is identified, the researcher can administer necessary treatment measures considering the subject’s condition, such as dose adjustment or temporary suspension of research drug usage. The decision regarding whether to terminate the study will depend on the circumstances. In case of an SAE occurrence, immediate action must be taken by the researcher to safeguard the safety of the subjects.

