### Sample size

In this study, the primary efficacy endpoint was the 28-day all-cause mortality rate. A large-scale epidemiological survey conducted in the ICU revealed that the control group had a 38.2% 28-day all-cause mortality rate. In an RCT comparing the LA injection treatment group, the relative risk reduction was approximately 0.33.^38^ The anticipated 28-day all-cause mortality rate for the treatment group was expected to be 22.9% with a one-sided test, using α=0.025 and β=0.2 (power=80%). The threshold value, Δ, was set at 0.

Participants are randomised at a ratio of 1:1, resulting in a calculated sample size of 160 for each group using a superiority test (where a lower rate is considered superior). Taking into account the anticipated dropout rate of around 10%, the sample size was increased to 176 cases in each group.

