### Statistical analysis

All analyses, including the primary analyses, will be conducted in accordance with the ITT principle. The data will be analysed using R software V.3.3.3 (R Foundation for Statistical Computing, Vienna, Austria) and RStudio V.1.0.136 (RStudio, Boston, MA, USA). Descriptive statistics will be used to describe the data’s distribution, with continuous data presented as mean (SD) or median and IQR, depending on the data characteristics. Categorical data will be reported as number and percentage. Group comparisons will be conducted using group t-tests or analysis of variance for continuous data assuming normality, and non-parametric tests will be used if normality assumptions are not met. Categorical results will be compared using χ^2^ test or Fisher’s exact test. The statistical significance level for all tests will be set at a p value of less than 0.05.

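### D3, D5 and D7 scores, lactate and biomarkers have no value after death, so the planned tests on observed values cannot be ITT unless death is built into the endpoint

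*Protocol article*

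**What the plan says.** In the protocol article, Evaluation and outcomes describes the data collection: "Follow-up values on specific days (day 1 (D1), D3, D5, D7) after randomisation will also be recorded, along with the changes from baseline". The endpoint list in the same section then makes the D1, D3, D5 and D7 values of SOFA, APACHE II, arterial lactate, PCT, hs-CRP and six cytokines secondary efficacy endpoints, both as levels and as changes from baseline. The cytokines need not be measured where the assay is unavailable.

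Statistical analysis says "All analyses, including the primary analyses, will be conducted in accordance with the ITT principle". For continuous data it names t-tests or ANOVA, with non-parametric tests if normality fails. Analyses sets and Intention-to-treat set (ITTS) define ITT as every randomised patient, in the assigned group, whether or not the trial was completed.

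Sample size gives the mortality that the trial plans for: "the control group had a 38.2% 28-day all-cause mortality rate", and "The anticipated 28-day all-cause mortality rate for the treatment group was expected to be 22.9% with a one-sided test". There are 176 patients per arm after the dropout allowance.

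The article gives no rule for a patient who dies before a measurement day. It also does not say that only available values will be compared.

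**The concern.** Three statements do not fit together. The endpoints are measurements on a fixed day, the analysis is promised on all randomised patients, and the tests named work on observed numbers. A patient who dies on D2 contributes nothing to a t-test of D7 SOFA. Followed as printed, the comparison is between the survivors of each arm, under an ITT label.

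This would matter less if deaths were equal by arm, but the trial is sized on the expectation that they are not. If LA keeps sicker patients alive, they remain in the LA mean while comparable placebo patients drop out of theirs. Suppressing inflammation and limiting organ dysfunction are stated aims in the Introduction, and these are the endpoints that address them. They could look neutral or unfavourable partly because the drug prevents deaths.

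**Working it through.** **Inputs from the article.** Control mortality 0.382, LA mortality 0.229, 176 patients per arm (Sample size). The article has no figure of its own for missing D3 to D7 values, so there is none to reproduce.

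**Inputs assumed.** The article does not give the share of 28-day deaths that occur by D7 or the correlation ρ between marker and early death. The table uses 25%, 50% and 67% for the share and 0.3, 0.5 and 0.7 for ρ.

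**Step 1: expected 28-day deaths.** Placebo: 176 × 0.382 = 67.2. LA: 176 × 0.229 = 40.3.

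**Step 2: shift in survivor means with no true marker effect.** Let severity be standard normal. A patient dies by D7 if severity exceeds the cut-off z that gives the early death proportion p. The survivor mean of a marker with correlation ρ to severity is then −ρ·φ(z)/(1−p), in SD units. The LA-minus-placebo difference is

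ρ × [φ(z_c)/(1−p_c) − φ(z_t)/(1−p_t)],

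where c is placebo, t is LA, and a positive value means worse on LA.

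Worked case, half of deaths by D7:
- Placebo: p_c = 0.1910, z_c = 0.874, φ = 0.2722, and 0.2722/0.8090 = 0.3365.
- LA: p_t = 0.1145, z_t = 1.203, φ = 0.1935, and 0.1935/0.8855 = 0.2185.
- Difference 0.1180, so the shift is 0.059 SD at ρ = 0.5 and 0.083 SD at ρ = 0.7.

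| Deaths by D7 | No D7 value, placebo vs LA | Bracket | ρ = 0.3 | ρ = 0.5 | ρ = 0.7 |
|---|---|---|---|---|---|
| 25% | 17 vs 10 | 0.1876 − 0.1218 = 0.0658 | 0.020 | 0.033 | 0.046 |
| 50% | 34 vs 20 | 0.3365 − 0.2185 = 0.1180 | 0.035 | 0.059 | 0.083 |
| 67% | 45 vs 27 | 0.4305 − 0.2784 = 0.1521 | 0.046 | 0.076 | 0.106 |

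At ρ = 0 every entry is zero.

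**Step 3: effect on the test.** In simulated trials of 176 per arm with no marker effect and half of deaths by D7, the two-sided 5% survivor-only t-test rejects in about 8% of trials at ρ = 0.5 and 12% at ρ = 0.7, nearly always towards harm. With 25% of deaths by D7 and ρ = 0.3, rejection stays close to 5%.

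**Step 4: levels against changes.** A second simulation assumed baseline SOFA with mean 8 and SD 3, change with mean −2 and SD 3, no true SOFA effect, and half of deaths by D7. The LA-minus-placebo differences among survivors, in points, were:

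| Early death depends on | D7 level | Change from baseline |
|---|---|---|
| baseline and change | +0.33 | +0.16 |
| baseline only | +0.19 | 0 |
| change only | +0.19 | +0.19 |
| neither | 0 | 0 |

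So the shift in change scores is smaller whenever baseline severity drives part of the mortality, and it matches the shift in levels only if baseline plays no part.

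**Step 5: sensitivity to the planned LA rate.** The article also says that "the relative risk reduction was approximately 0.33". Applied to 38.2%, that gives 0.382 × 0.67 = 25.6%, not 22.9%. With 25.6% and half of deaths by D7, p_t = 0.128 and its term is 0.2400. The bracket becomes 0.3365 − 0.2400 = 0.0965, or 0.048 SD at ρ = 0.5 instead of 0.059. The imbalance is smaller but remains.

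**The case against.** The strongest reply is that this is detail for the statistical analysis plan. A journal article names families of tests, and the handling of death may be set out in a document not shown. The printed text even permits a non-parametric test, so a rank test with death placed worst would comply with it. The ITT definition excludes no such rule. This stands as a limit: the conflict disappears once death is built into the endpoint. It does not remove the point, because the article promises ITT for every analysis while defining endpoints that some randomised patients cannot have.

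A reader might infer more than the article supports:
- **That these endpoints can never be derived for everyone.** A death rule would give each patient a result.
- **That the plan states a comparison of survivors only.** That is how the named tests act on observed values; the article does not say it.
- **That the comparison is necessarily biased against LA.** The direction requires that the patients saved have worse markers. For cytokines such as IL-4, IL-10 and IFN-γ the article fixes no worse direction.
- **That D1 is affected in the same way.** Few deaths would be expected by then.
- **That ranking death worst is simply a more powerful test of the same effect.** It responds to mortality itself. With no marker effect, half of deaths by D7 and ρ = 0.5, it rejects in about 13% of simulated trials.

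It is also fair that only secondary endpoints are involved, and that mortality is reported alongside them.

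**Conclusion.** The point holds in limited form. For D3, D5 and D7, the named tests on observed values cannot deliver the ITT analysis that the article promises, unless death is made part of the endpoint or the analysis is labelled as conditional on survival. Under the planned mortality the loss is unequal by arm.

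If the patients saved are sicker, mean scores and lactate shift against LA by about 0.02 to 0.11 SD. That range rests on 25% to 67% of deaths falling by D7, a correlation of 0.3 to 0.7 and the normal model above. At the low end the distortion would hardly be noticed; at the high end it is enough to mislead. The primary endpoint, 28-day all-cause mortality, is not touched. The wording should be corrected before unblinding, but the main result is not threatened.

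**What to change.** - **SOFA and APACHE II on D3, D5 and D7:** compare all randomised patients with a rank-based test (Wilcoxon or proportional odds) in which death on or before that day is the worst rank. Describe it as a combined death and organ-function endpoint, and show the survivor-only summary beside it.
- **Lactate, PCT, hs-CRP and the cytokines:** withdraw the ITT claim and label the results as applying to patients alive and sampled. Give the numbers dead, discharged and sampled by arm and day.
- **Statistical analysis section:** limit the statement that all analyses follow ITT accordingly.

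The cost is wording only, with no new data, visits or patients. The drawback is that the ranked endpoint also moves with mortality. It is not a pure test of organ function and should not be presented as a more powerful version of the survivor comparison.

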**Methods and analysis:**

A total of 352 sepsis patients are planned to be recruited from intensive care units (ICUs) at eight tertiary hospitals in China for this trial. Eligible participants will undergo randomisation in a 1:1 ratio, allocating them to either the control group or the experimental group. Both groups received routine care, with the experimental group also receiving lipoic acid injection and the control group receiving placebo. The primary efficacy endpoint is 28-day all-cause mortality. The secondary efficacy endpoints are as follows: ICU and hospital mortality, ICU and hospital stay, new acute kidney injury in ICU, demand and duration of life support, Sequential Organ Failure Assessment (SOFA)/Acute Physiology and Chronic Health Evaluation II (APACHE II) and changes from baseline (ΔSOFA/ΔApache II), arterial blood lactate (LAC) and changes from baseline (ΔLAC), blood procalcitonin, high-sensitivity C-reactive protein, interleukin-2 (IL-2), IL-4, IL-6, IL-10, tumour necrosis factor-α (TNF-α) and interferon-γ (IFN-γ) and changes from baseline on day 1 (D1), D3, D5 and D7. Clinical safety will be assessed through analysis of adverse events.

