## Methods and analysis

### Study design and setting

The ALIS (‘Adjuvant Lipoic acid Injection in Sepsis treatment in China’) study is a multicentre, single-blind, randomised, placebo-controlled clinical trial conducted in tertiary hospitals in China. The protocol and informed consent forms are required to undergo a thorough review and approval by the applicable ethical committees (ECs) to ensure compliance with scientific standards and human subject protection regulations at each participating centre. The study involves various departments, including general ICU, neurological ICU, surgical ICU and emergency ICU. Detailed information about the intended participating centres can be found in table 1. The enrolment period for this study is estimated to be 2 years, and the trial will conclude with the last follow-up. The study has been registered,^35^ ensuring transparency and accessibility of the study information. The study design and protocol adhere to the Standard Protocol Items: Recommendations for Interventional Trials reporting guidelines.^36^

**Table 1 T1:** Research settings and names of each ethics committee

Research setting	Ethics committee name	Hospital rank and location
Maoming People’s Hospital	Medical Ethics Committee of Maoming People’s Hospital	Tertiary, Maoming, Guangdong, China
Guangdong Provincial People’s Hospital	Medical Ethics Committee of Guangdong Provincial People’s Hospital	Tertiary, Guangzhou, Guangdong, China
Affiliated Hospital of Guangdong Medical university	Medical Ethics Committee of Affiliated Hospital of Guangdong medical university	Tertiary, Zhanjiang, Guangdong, China
Central People’s Hospital of Zhanjiang	Medical Ethics Committee of Central People’s Hospital of Zhanjiang	Tertiary, Zhanjiang, Guangdong, China
Huizhou Central Hospital	Medical Ethics Committee of Huizhou Central Hospital	Tertiary, Huizhou, Guangdong, China
Xiaolan People’s Hospital of Zhongshan City	Medical Ethics Committee of Xiaolan People’s Hospital of Zhongshan	Tertiary, Zhongshan, Guangdong, China
Third People’s Hospital of Huizhou	Medical Ethics Committee of the Third People’s Hospital of Huizhou	Tertiary, Huizhou, Guangdong, China
Yunfu People’s Hospital	Medical Ethics Committee of Yunfu People’s Hospital	Tertiary, Yunfu, Guangdong, China

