### Eligibility criteria

All trial centres will adhere to the same participant inclusion criteria. The inclusion criteria are as follow:

Meeting the diagnostic criteria for sepsis and septic shock, as established by the American Critical Care Medical Association/European Critical Care Medical Association (Sepsis-3 criteria).^37^Age between 18 and 80 years.Within 48 hours of receiving a diagnosis of sepsis or septic shock.Having provided signed informed consent.

The exclusion criteria for participant selection are as follows:

Female patients who are pregnant or lactating.Presence of persistent infection sources that cannot be effectively eliminated through procedures such as puncture, drainage, debridement, or other surgical operations.Participation in another clinical trial.Current treatment with other medications that have antioxidant effects, such as vitamin C and vitamin E.Accompanied by non-infectious but life-threatening conditions, such as advanced tumour, severe craniocerebral injury, uncontrollable massive bleeding, cardiogenic shock, etc.Lack of approval for comprehensive and active life support treatment.Allergy to LA or similar active agents (eg, vitamin B), or previous intolerance to the recommended dose of LA.

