#### Intention-to-treat set (ITTS)

The principle of ITT analysis is adopted to retain the randomised information effectively and attribute differences in trial results to treatment variations. This ensures that the assessment of treatment effects, specifically in the case of LA treatment, is conducted in the most accurate manner possible. The ITT set (ITTS) consists of all patients who were randomised, regardless of whether they received their designated treatment or completed the full trial. All patients in the ITTS remain in their original assigned groups for analysis. By adhering to the ITT principles, the analysis maintains the integrity of the randomisation process and provides a comprehensive evaluation of the treatment’s effectiveness, accounting for the real-world scenario.

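### New AKI is counted from ICU admission rather than from randomisation, so kidney injury arising in the ICU before randomisation enters a secondary endpoint and dilutes any treatment effect

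*Protocol article*

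**What the plan says.** Under Evaluation and outcomes, the article lists among the prognosis data "incidence of new-onset acute kidney injury (AKI) after ICU admission". The secondary endpoint list in the same section calls it the incidence of new AKI in ICU, and the abstract lists "new acute kidney injury in ICU". None of the three mentions randomisation or first dose.

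The repeated measures are handled differently in the same section: "Follow-up values on specific days (day 1 (D1), D3, D5, D7) after randomisation will also be recorded".

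Three other places determine who can have AKI before treatment:

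- Study design and setting: "The study involves various departments, including general ICU, neurological ICU, surgical ICU and emergency ICU".
- Eligibility criteria: entry is allowed "Within 48 hours of receiving a diagnosis of sepsis or septic shock". That clock starts at diagnosis. Nothing limits the time already spent in the ICU, and no exclusion concerns existing AKI.
- Statistical analysis: "All analyses, including the primary analyses, will be conducted in accordance with the ITT principle". Under Analyses sets, "The ITT set (ITTS) consists of all patients who were randomised". No separate at-risk set is named for AKI.

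**The concern.** A randomised comparison measures what happens after allocation. An outcome clock that starts at ICU admission also collects events from the interval between admission and randomisation. Here that interval can be real, because patients are recruited in the ICU, may be up to two days past diagnosis, and may have been in the ICU before the diagnosis was made.

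AKI in that interval is new and occurs in the ICU, so it satisfies the wording. Treatment cannot have prevented it. Randomisation spreads these events evenly in expectation, so they create no spurious benefit or harm. They add the same amount to both arms and move the risk ratio towards 1.

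At stake is the trial's ability to show a renal effect if one exists. Reducing organ dysfunction is a stated aim in the Introduction, and AKI is the only endpoint on the list that is framed as new-onset failure of a specific organ.

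**Working it through.** The article states no AKI rate, AKI effect or AKI power, so there is no figure of its own to reproduce. What follows shows the mechanism under labelled assumptions.

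**Inputs**

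- Arm size 176, from Sample size ("the sample size was increased to 176 cases in each group").
- True risk ratio on post-randomisation AKI of 0.67. Assumed: it borrows the relative risk reduction of about 0.33 that Sample size gives for mortality.
- Two-sided 0.05. The article gives 0.05 for all tests; two-sided is assumed.
- The amount of AKI before randomisation and the AKI risk after it. Both assumed.

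**Step 1: dilution of the risk ratio**

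Let s be the share of control-arm AKI, as the endpoint is written, that arises before randomisation. Let the control incidence be 40% (assumed). The pre-randomisation part, 0.40 × s, is the same in both arms; treatment acts only on the rest.

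Treated incidence = 0.40 × s + 0.67 × 0.40 × (1 − s)

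Observed RR = s + 0.67 × (1 − s), in which the 40% cancels.

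| s | Control | Treated | Observed RR |
|---|---|---|---|
| 0 | 0.400 | 0.268 | 0.67 |
| 0.2 | 0.400 | 0.080 + 0.214 = 0.294 | 0.74 |
| 0.4 | 0.400 | 0.160 + 0.161 = 0.321 | 0.80 |
| 0.6 | 0.400 | 0.240 + 0.107 = 0.347 | 0.87 |

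**Step 2: does restricting to patients at risk cost more than it gains?**

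Let q be the proportion of all patients with ICU-onset AKI before randomisation. Let the control risk afterwards, in those still free of AKI, be pc = 0.30 (assumed), so the treated risk is pt = 0.67 × 0.30 = 0.201.

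- As written: risk = q + (1 − q) × p, with 176 per arm.
- Re-anchored: risk = p, with 176 × (1 − q) per arm.

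Power uses the normal approximation for two proportions, pooled variance under the null and unpooled under the alternative.

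| q | As written, control v treated | RR | Power as written | RR re-anchored | Power re-anchored |
|---|---|---|---|---|---|
| 0 | 30.0% v 20.1% | 0.67 | 57% | 0.67 | 57% |
| 0.1 | 37.0% v 28.1% | 0.76 | 43% | 0.67 | 53% |
| 0.2 | 44.0% v 36.1% | 0.82 | 33% | 0.67 | 48% |
| 0.3 | 51.0% v 44.1% | 0.86 | 25% | 0.67 | 43% |
| 0.5 | 65.0% v 60.1% | 0.92 | 16% | 0.67 | 33% |

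For pc from 0.20 to 0.40 and q from 0.1 to 0.5, the observed RR runs from 0.74 to 0.95. The re-anchored analysis had more power at every non-zero q tried, despite the smaller denominator. For example, at q = 0.3 it has 59% against 41% with pc = 0.40, and 28% against 14% with pc = 0.20.

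**Step 3: AKI already present at ICU admission**

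These patients are a different case. Their AKI is not new, so they are non-events. If a proportion b of each arm is of this kind and stays in the denominator, both risks are multiplied by (1 − b). The risk difference shrinks by that factor, but the RR is unchanged. The dilution in Steps 1 and 2 comes only from ICU-onset AKI before randomisation.

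**The case against.** The strongest reply is that the explicit phrase about ICU admission stands in a list of data to be collected. The endpoint list names only a setting and the word new. The same section says that AKI is monitored throughout the study, which could mean ascertainment from enrolment on. The article is condensed, its supplementary assessment schedule is not shown, and onset rules for a secondary endpoint often sit in a fuller document.

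Part of this stands: an operational definition may exist elsewhere. But the only time origin that the article gives for AKI is ICU admission, and it uses randomisation a few lines earlier for the repeated measures. That is a stated anchor, not an omitted detail.

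It is also fair that the size is unknown. Patients randomised soon after ICU admission contribute little or no dilution, and the 48-hour limit does not show how long anyone had been in the ICU.

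Some stronger readings are tempting but not supported:

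- A reader might infer that patients who die early without AKI are counted as successes. The article does not say how deaths are handled for this endpoint.
- A reader might take an all-patient denominator for AKI as stated. It is an inference from the general ITT text, not part of the AKI wording.
- A reader might extend the point to ICU stay and life-support durations. The article gives no time origin for these, so it cannot be said that they are wrongly anchored.

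**Conclusion.** The point holds for the time origin. As worded, AKI that arises in the ICU before randomisation counts as an outcome that treatment cannot influence. The effect on this endpoint is attenuation towards no difference, not a false signal in either direction.

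Under the assumed shares of 20%, 40% and 60%, a true RR of 0.67 would appear as 0.74, 0.80 and 0.87. With a share of zero nothing is lost. These figures rest on an effect size borrowed from mortality and on shares that the documents do not give, so they show direction and plausible scale, not an estimate for this trial. Even re-anchored, the AKI comparison remains modestly powered under most of the assumptions tried.

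The 28-day mortality primary endpoint is unaffected. The change is worth making because the wording is at odds with the rest of the outcome schedule and is easy to correct.

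**What to change.** Define the secondary endpoint as AKI with first onset after randomisation, analysed among patients without AKI at randomisation, each kept in the assigned arm. The subset is fixed by status before allocation takes effect, so the randomised comparison is preserved. Use the same wording in the abstract, the data description and the endpoint list.

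Take baseline AKI status from the kidney biochemistry that the article already lists, and report its frequency by arm. The sponsor should confirm that a suitable value is available at randomisation. The article does not mention urine output, so the definition should not assume that it is recorded.

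AKI or death by day 28 may be added as a supportive analysis, so that the AKI result can be read alongside mortality.

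The cost is a wording change and a smaller at-risk denominator. With q = 0.2, for example, about 140 patients per arm remain of 176.

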### Participant timeline

The follow-up period for this trial is 28 days. At the final visit of the last patient, data regarding the clinical status of all participants who have either completed the trial or withdrawn will be collected.

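### Raw durations of stay and life support are compared by t-test or rank test although death ends them, so these secondary comparisons are confounded by mortality in a direction that cannot be known in advance

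*Protocol article*

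**What the plan says.** All references are to the protocol article.

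- **Evaluation and outcomes** lists, as secondary efficacy endpoints, the durations of ICU and hospital stay and "Demand and duration of life support measures (vasopressors, invasive mechanical ventilation and continuous renal replacement therapy"). No free-day measure is listed, and no value is assigned to a patient who dies.
- **Statistical analysis** fixes the method: "Group comparisons will be conducted using group t-tests or analysis of variance for continuous data assuming normality", with non-parametric tests where normality fails. It places every analysis under intention to treat. **Analyses sets** keeps all randomised patients in their assigned groups, so patients who die stay in these comparisons.
- **Sample size** assumes that "the control group had a 38.2% 28-day all-cause mortality rate", with the LA rate "expected to be 22.9% with a one-sided test, using α=0.025 and β=0.2 (power=80"%).
- **Participant timeline** states "The follow-up period for this trial is 28 days". It adds that clinical status is collected for all participants at the last patient's final visit.
- **Introduction** names a shorter ICU or hospital stay among the trial's aims, so a short duration is read as benefit.

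**The concern.** Death ends a period of ventilation, vasopressor use, CRRT, ICU stay or hospital stay just as recovery does. In a raw comparison a patient who dies on day 3 contributes a short duration, and short is the favourable direction. Changing to a rank test does not help, because the early death still ranks among the good results.

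The trial is designed to detect a large mortality difference, so the arms are expected to differ in how many durations death cuts short. The raw comparison then mixes two effects: the drug's effect on speed of recovery and its effect on survival. If patients who die do so sooner than survivors recover, a life-saving drug appears to prolong support. If they die later, the same drug appears to shorten it. In neither case can the duration result be read as an effect on recovery.

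**Working it through.** **Plan figures used.** "Participants are randomised at a ratio of 1:1, resulting in a calculated sample size of 160 for each group", then the 10% dropout step: 160 × 1.1 = 176 per arm, 352 in total, as stated. Mortality is 38.2% on control and 22.9% on LA.

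**Expected deaths, all randomised patients analysed.**
- Control: 176 × 0.382 = 67.2, about 67.
- LA: 176 × 0.229 = 40.3, about 40.
- Difference: about 27 more control durations ended by death.

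**Assumptions not in the documents.** Time to death in those who die and time to recovery in survivors are log-normal with log-SD 0.8, capped at day 28. The medians are varied below. LA changes survival only, and survivors' recovery time has the same distribution in both arms. A true duration effect is therefore absent by construction.

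**Mean raw duration.** Write D and R for the capped mean times to death and to recovery, and p for mortality.

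- Arm mean = p·D + (1 − p)·R.
- LA minus control = (0.382 − 0.229)·(R − D) = 0.153·(R − D).

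The sign is the sign of R − D, so direction depends wholly on relative timing. For median m, the capped mean is m·exp(0.8²/2)·Φ(a − 0.8) + 28·[1 − Φ(a)], where a = ln(28/m)/0.8. This gives 4.11, 6.72, 9.11, 12.23 and 15.56 days for medians 3, 5, 7, 10 and 14.

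Example, medians 3 (death) and 7 (recovery):
- Control: 0.382 × 4.11 + 0.618 × 9.11 = 7.2 days.
- LA: 0.229 × 4.11 + 0.771 × 9.11 = 8.0 days.

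**Support-free days to day 28, death scored 0.** Arm mean = (1 − p)·(28 − R). With median recovery 7: control 0.618 × 18.89 = 11.7, LA 0.771 × 18.89 = 14.6.

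**Simulated trials.** 176 per arm, 1,000 trials per row, two-sided 5% Mann–Whitney test on the same data scored both ways.

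| Median death / recovery (days) | Mean raw duration, control vs LA | LA significantly longer | LA significantly shorter | Mean free days, control vs LA | Free days significantly better on LA |
|---|---|---|---|---|---|
| 3 / 7 | 7.2 vs 8.0 | 28% | 0% | 11.7 vs 14.6 | 69% |
| 5 / 7 | 8.2 vs 8.6 | 9% | 0.4% | 11.7 vs 14.6 | 69% |
| 5 / 10 | 10.1 vs 11.0 | 20% | 0.2% | 9.7 vs 12.2 | 65% |
| 5 / 14 | 12.2 vs 13.5 | 34% | 0% | 7.7 vs 9.6 | 57% |
| 7 / 7 | 9.1 vs 9.1 | 3.0% | 3.3% | 11.7 vs 14.6 | 67% |
| 10 / 7 | 10.3 vs 9.8 | 0.7% | 8.8% | 11.7 vs 14.6 | 67% |

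Free days were never significantly worse on LA in any row. The 7 / 7 row shows rejection close to the nominal 2.5% on each side, which is what no bias looks like.

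**Sensitivity to the mortality assumption.** The Sample size section also says "the relative risk reduction was approximately 0.33", which would give 0.382 × 0.67 = 25.6% on LA rather than 22.9%. The multiplier 0.153 becomes 0.126, so each mean shift shrinks by about a fifth (0.126 / 0.153 = 0.82). The pattern does not change. That inconsistency is a separate matter.

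**The case against.** **The statistical analysis plan may handle it.** The methods paragraph is generic, and rules for deaths in secondary durations are often left to the SAP, which is not shown. The article does not say that an early death counts as a short value; that follows from intention to treat plus the absence of another rule. This is fair as far as it goes. What stands is what the article does fix: the endpoint is a duration, all randomised patients are analysed, and none of the named tests accounts for death.

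**Mortality is reported alongside.** A reader would see 28-day, ICU and hospital mortality next to any longer stay, and the primary endpoint is untouched. This lowers the severity. It does not make the duration comparison interpretable.

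**Restricting to survivors would avoid the problem.** The article does not state this restriction. It would compare about 109 control with 136 LA patients, groups selected after randomisation by an outcome that treatment is expected to change.

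**Stronger readings that the documents do not support.**
- A reader might infer that the durations are biased against LA whenever LA lowers mortality. The last two rows of the table show otherwise.
- A reader might infer that hospital stay and hospital mortality cannot be fully observed within 28 days. Status is also collected at the last patient's final visit, which for most patients may fall after day 28. The supportable point is only that the horizon is unclear.
- A reader might extend the argument to SOFA and APACHE II on days 3 to 7. The article does not say that patients who have died are dropped from those comparisons. That is missing-data detail commonly left to the SAP.

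**Conclusion.** The concern holds for the secondary durations of stay and life support. As fixed in the article, these comparisons are confounded by mortality, with about 67 against 40 deaths expected at 176 per arm, and can be biased in either direction.

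The size rests on assumed timings. With median recovery at least twice median time to death, 20–34% of trials would call a purely life-saving drug significantly longer. With the closer medians of 5 and 7 days it is about 9%. With equal medians the bias vanishes, and with deaths later than recovery it reverses. None of these percentages is a prediction for this trial. The firm conclusion is the confounding itself, since its direction cannot be determined from the documents.

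This should be fixed. It does not threaten the 28-day mortality analysis.

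**What to change.** 1. Keep the listed durations, but present them descriptively, overall and by survival status.
2. Base between-group inference on days alive and free of ventilation, vasopressors, CRRT, ICU and hospital, each counted from randomisation to day 28, with death by day 28 ranked worst. Compare by a rank test or a proportional-odds model.
3. Optionally show time to discharge alive, with death as a competing event.
4. State the time horizon for hospital stay and hospital mortality: day 28, or discharge whenever it occurs.

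**Cost.** Mostly analysis wording. It does change how listed secondary endpoints are tested in a trial that has been recruiting since August 2021, so it should be recorded as an amendment before any unblinded comparison; no interim analysis is planned. The composite is slightly harder to describe than a length of stay and partly overlaps the mortality endpoint. The article says that the requirement for and duration of support are recorded, but does not mention start, stop or restart dates. The sponsor should therefore first confirm that free days can be derived from what is collected.
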